### Sample Size

The sample size for this study was generated from effect sizes found in other studies on MCP in participants with cancer, mainly meta-analyses. Dietrich (29) found medium effect sizes for meaning in life (*d* = 0.81), Quality of life (*d* = 0.60), anxiety (*d* = −0.47), and depressive symptoms (*d* = −0.50). These effect sizes are consistent with other studies on MCP in psychological treatments for other mental disorders, such as a meta-analysis by Vos et al. (12) on existential psychotherapies. Based on the results of these studies, we expect an effect size of 0.60 because the study design consists of two experimental groups. To calculate the sample size, we used the G^*^Power 3.1 software (30), taking into account an alpha of 0.05 and a statistical power of 0.80 on a two-tailed *t*-test. We need a sample size of 90 participants (45 participants per condition) to reach an effect size of 0.60 for meaning in life. Finally, we have considered possible sample loss during the treatment program, and based on studies of interventions with MCP, we expect a 30% dropout rate (9). Therefore, taking this outcome into account, our study requires a total sample size of 118 participants (59 participants per experimental condition).

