### Procedure

Cancer survivors who have been treated at the Valencian Institute of Oncology will be offered the opportunity to participate in the study. Once they have signed the informed consent, a clinical psychologist who is an expert in cancer will carry out two evaluation sessions to verify that they meet all the inclusion criteria. Once evaluated, randomization will be carried out by an independent researcher who is blind to the evaluation of the participants. At all times, the randomization sequence will be concealed from the clinicians participating in the study. The evaluation will be carried out by independent evaluators who are blind to the experimental conditions. Subsequently, each participant will begin their group intervention in the condition to which they have been assigned. Participants will not receive any other psychological or psychiatric treatment during this study. When the psychotherapy is over (MCP or CBT), the evaluation will be carried out again. A follow-up will be carried out at 1 month, at 3 months, and at 6 months. The evaluation will be carried out online before and after finishing the treatment and in the follow-ups. All the interventions will be performed by clinical psychologists or general health psychologists with a Master's degree and previous training in the application of the programs. All the interventions will be carried out through online video conferences in both treatment conditions.

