### Interventions

#### Meaning-Centered Group Psychotherapy

To carry out the adaptation of the Manualized Meaning-Centered Group Psychotherapy (MCP) group format for patients with advanced cancer (32) to Spanish, we used the ecological validity model (EVM) (33) as a framework for the cultural adaptation of MCP to respond to the needs of the Spanish population with cancer. According to the EVM, to adapt an intervention for a new cultural group, seven dimensions need to be addressed: language, context, persons, metaphors, concepts, goals, and methods. We first carried out a translation of the original MCP program from English to Spanish. The translation was performed by two bilingual clinical psychologists who are experts in meaning-focused psychotherapy; this translation was supervised by a bilingual editor with expertise in clinical psychology. A feasibility study (in preparation) with 12 participating cancer survivors was conducted by two clinical psychologists who are experts in cancer. Finally, we tested the understanding, acceptance, and feasibility of the Spanish version of the MCP with a qualitative interview and questionnaires. The intervention lasts 2 months and includes 8 sessions that follow a 2-h group format on a weekly basis. We will follow the manualized MCP for patients with advanced cancer (32). The MCP program is divided into 8 sessions:

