### Data Analyses

For data analysis, the Consort guidelines will be followed. Prior to analyzing whether MCP was more effective than CBT, we will verify that the two experimental conditions are similar in all the sociodemographic variables, such as age, sex, marital status, and education. In addition, we will verify that the two conditions are similar in terms of the percentage of participants who have received chemotherapy, radiotherapy, and surgery. To do so, we will use comparison of means (Student's t) for the continuous variables and chi square for the categorical variables. Moreover, the intention-to-treat principle will be used when analyzing pre- and post-treatment data and at the 6-month follow-up, using mixed-effects models with full information and maximum likelihood estimation. This method has been recommended due to its flexibility in handling missing data (51). To complement the MANOVA results and *post hoc* comparisons, effect sizes will be calculated using the standardized mean difference proposed by Cohen (52). These effect sizes will be calculated to assess changes within and between groups, all based on a pooled standard deviation. MANCOVAS will be carried out to find out if there are differences in the participants' response to the two experimental conditions depending on the type of medical treatment administered (surgery, chemotherapy, or radiotherapy), the stage of the cancer before the start of medical treatment, and whether the patient has a relapse during the psychological treatment. Moderation and mediation analyses will be performed to investigate possible mediators of change during treatment, such as meaning in life or coping style. Although per-protocol analyses (only analyses of data from participants who complete the treatment) suffer from selection bias, they will also be conducted because they allow conclusions to be drawn about the maximum efficacy of the intervention in participants who are fully compliant with treatment. However, when the trial is completed, the analytical methodology for controlled clinical trials will be reviewed before analyzing the data to select the most appropriate analytical procedures.

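### Both therapies are delivered in groups, but the sample size of 45 per arm makes no allowance for therapy-group clustering, so the 80% power stated for that calculation is overstated

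*Protocol article*

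**What the plan says.** Participants are randomised individually (Study Design). The Procedure section then states that "each participant will begin their group intervention in the condition to which they have been assigned". The MCP section describes a programme that "includes 8 sessions that follow a 2-h group format on a weekly basis", and the CBT section repeats that format. The Ethics section adds that two psychologists deliver the intervention.

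The Sample Size section expects an effect size of 0.60 and uses "an alpha of 0.05 and a statistical power of 0.80 on a two-tailed" t-test in G*Power. It concludes: "We need a sample size of 90 participants (45 participants per condition) to reach an effect size of 0.60 for meaning in life". It then adds an allowance for 30% dropout and arrives at 118 (59 per arm). It mentions no group size, number of groups, ICC or design effect.

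The Data Analyses section plans an intention-to-treat analysis "using mixed-effects models with full information and maximum likelihood estimation". The only reason given for this choice is its handling of missing data. MANOVA results and MANCOVAs appear alongside. No random effect of any kind is named, and the section ends by leaving the methods open to review once the trial is complete.

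**The concern.** Members of a therapy group share about 16 hours of contact (8 x 2 h), a therapist and one another's contributions, so their outcomes after treatment may be correlated even though they were randomised one by one. A positive correlation inflates the variance of each arm's mean by the design effect. There are two consequences, and the document supports them to different degrees.

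- **Power.** The sample-size calculation is printed with its inputs and treats participants as independent. This is a stated figure, not a detail that could be waiting in an analysis plan.
- **Inference.** If the analysis also ignores therapy groups, the intervals for MCP versus CBT are too narrow and the type I error exceeds 5% wherever the ICC is positive. This depends on a modelling choice that the article leaves open.

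The comparison affected is the trial's first objective.

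**Working it through.** **Inputs from the Sample Size section:** d = 0.60, two-sided alpha 0.05, 45 analysable per arm.

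**Assumptions, because the article gives no values:** group size m = 6 to 12 and ICC = 0.01 to 0.10, the same in both arms.

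**1. Reproduce the stated figure.** Two-sample t-test with the noncentral t distribution, noncentrality d x sqrt(n/2), df = 2n - 2:
- n = 45: 0.60 x sqrt(22.5) = 2.85, df 88, power 0.804.
- n = 44: power 0.795.

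So 45 is the smallest n that reaches 80% with independent data. A design effect of 45/44 = 1.023 uses up the margin; at 8 per group that is an ICC of 0.023/7, about 0.003.

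**2. Add clustering.** DE = 1 + (m - 1) x ICC, effective n = 45/DE, noncentrality = 0.60 x sqrt(45/(2 x DE)). Power is computed with individual-level df (88) and, more strictly, with group-level df = 2 x (45/m - 1).

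Example, m = 8 and ICC = 0.05: DE = 1 + 7 x 0.05 = 1.35; effective n = 45/1.35 = 33.3; noncentrality = 2.45; power 0.68 with 88 df, and 0.59 with 2 x (5.625 - 1) = 9.25 df.

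**3. Type I error if therapy group is ignored.** 2 x P(t with 88 df > 1.987/sqrt(DE)). In the example, 1.987/sqrt(1.35) = 1.710, which gives 0.091.

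| m | ICC | DE | Power, 88 df | Power, group-level df | Type I error if group ignored |
|---|---|---|---|---|---|
| 6 | 0.01 | 1.05 | 0.78 | 0.73 | 0.056 |
| 6 | 0.10 | 1.50 | 0.63 | 0.58 | 0.108 |
| 8 | 0.05 | 1.35 | 0.68 | 0.59 | 0.091 |
| 12 | 0.01 | 1.11 | 0.76 | 0.60 | 0.063 |
| 12 | 0.10 | 2.10 | 0.49 | 0.37 | 0.174 |

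**4. Size needed for 80% with the same t-test.** Multiply 45 per arm by DE and round up. In the example, 45 x 1.35 = 60.75, so 61 per arm or 122 analysable. Over the range, 96 to 190 analysable. Group-level df would require more.

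**5. Does the dropout allowance give slack?** No. At the article's own 30% loss, 118 x 0.70 = 82.6, below the 90 required. Power at 41 per arm is already about 0.77 with independent data, and 0.64 in the example (individual-level df).

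**The case against.** The strongest objection concerns the analysis. A reader might infer that the planned mixed model treats participants as independent, so that its standard errors are too small. The documents do not support that. The Data Analyses section gives no random-effects structure, whether for participant, group or therapist. A mixed model can carry a therapy-group term, and a journal article commonly leaves that detail to the full protocol or analysis plan. The methods are also left open to review. This objection stands: too-small standard errors are conditional on omitting the term. What remains is that the text points that way, since missing data is the only justification given and MANOVA and MANCOVA, as usually run, are single-level.

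A second objection is that the power figures apply to an unadjusted t-test, whereas the planned model uses pre-treatment data. The Primary Outcomes section gives one-month test-retest coefficients of 0.70 and 0.73 for the MLQ subscales. As an illustration, take a pre-post correlation of 0.70, and group variance not explained by baseline. The example's variance factor is then (1 - 0.49 - 0.05) + 8 x 0.05 = 0.86, and power is about 0.86 (0.78 with group-level df). At a correlation of 0.50 the factor is 1.10 and power is 0.77 (0.68). So net power may fall on either side of 80%. This also stands, but the Sample Size section neither claims a baseline gain nor states a correlation, so it does not rescue the 80% as stated.

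A third objection is that group size and ICC are assumed. That is true. At the low end of the range, the type I error effect is negligible.

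**Conclusion.** The point holds for the sample size and conditionally for the analysis. The 45 per arm is an independent-samples calculation for a group-delivered trial, and any positive within-group correlation lowers its power from a starting point of 0.804. How far depends on assumed values: 0.78 to 0.49 for 6 to 12 per group and ICC 0.01 to 0.10 (0.73 to 0.37 with group-level df), and 0.68 (0.59) in the middle example. The power of the final baseline-using analysis cannot be fixed from this document.

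It does not follow that the trial's standard errors will be wrong. Type I error of about 0.056 to 0.174 (0.091 in the example) arises only if the therapy-group term is left out and the ICC lies in the assumed range. The closing promise to review methods does not settle the matter: it comes after the sample size is set, and it does not ensure that group membership is recorded.

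**What to change.** - **During delivery:** record a therapy-group identifier for every participant, and the therapist, since two psychologists deliver the treatment.
- **In Data Analyses:** name a random effect for therapy group within arm, acting on post-baseline outcomes only, because groups form after the baseline assessment. Fit by REML with Kenward-Roger or Satterthwaite degrees of freedom. Once a group term is in the model this matters: at 8 per group there are only about 45/8 = 5.6 groups per arm, and plain maximum likelihood understates variance components when groups are few.
- **In Sample Size:** restate power with an explicit group size, ICC and design effect. If a gain from baseline adjustment is to be counted, state the assumed pre-post correlation.

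The cost is one data column, one model term and a short revision of the power statement. The downside is wider intervals and a less favourable power figure, possibly well below 80%. The restated figure may show that 118 is too few: the example needs 122 analysable for the stated t-test, or about 175 randomised at 30% loss (122/0.70 = 174.3). If recruitment cannot be extended, the lower power should be reported as it is.

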### Ethics

The study involves clinical experimentation with human participants. Researchers adhere to the Helsinki Convention and the Madrid Declaration of the World Psychiatric Association on clinical research. This project has been approved by the Ethics and Research Committee of the Valencian Institute of Oncology Foundation (CEIM: 2019–17). The study was registered with Clinicaltrials.gov as NCT05197348. All participants will be volunteers and give their informed consent to participate in the study. All eligible participants will receive oral and written information about the study and the two intervention modalities. Specifically, they will be informed that they can leave the study at any time without any explanation, and that this decision will not affect the continuation of their usual treatment at the Valencian Institute of Oncology. The selection and evaluation of the participants will be carried out by a clinical psychologist who is blind to the condition assigned to the participants. The intervention will be carried out by two psychologists who specialize in cancer. In addition, it should be noted that the protocols for action and custody of the information followed in the Valencian Institute of Oncology, where the participants will be recruited and the interventions will be carried out, comply with all the requirements of the LOPD (Organic Law 15/1999, of December 13, 2018). In addition, based on the existing knowledge in this field, we have not found any risks to the participants. However, any important clinical change that involves some type of risk will not only imply the participant's termination in the study, but also his/her referral for study and specialized care. The evaluation protocol described above is composed of standardized and risk-free instruments for the participants (interviews and questionnaires). The intervention protocols are based on empirically validated treatments designed and developed by personnel with extensive knowledge and experience in this field. For ethical reasons, participants in the CBT condition will be offered the opportunity to receive the MCP program, if they so desire, even if the study has already ended.

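### The completer analysis cannot support the planned conclusion about maximum efficacy, because completers are selected after randomisation and the bias can run either way

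*Protocol article*

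**What the plan says.** The Data Analyses section of the protocol article sets the main approach: "the intention-to-treat principle will be used when analyzing pre- and post-treatment data and at the 6-month follow-up", using mixed-effects models fitted by maximum likelihood. It then adds a second analysis. It says that "per-protocol analyses (only analyses of data from participants who complete the treatment) suffer from selection bias", but that these analyses will be run as well because "they allow conclusions to be drawn about the maximum efficacy of the intervention in participants who are fully compliant with treatment".

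Three other places bear on who ends up in the completer set:

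- **Sample Size** expects 30% loss during the treatment programme and raises the target from 90 to 118 participants (59 per arm).
- **Discussion** (limitations) expects dropout in both treatment conditions and gives no rate by arm.
- **Ethics** lets participants leave at any time without giving a reason, and says that "any important clinical change that involves some type of risk" leads to termination in the study and referral.

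**The concern.** The sentence names a bias and then draws the conclusion that the bias rules out. Whether someone completes eight weekly sessions becomes known only after allocation, and it may depend on the therapy received and on how the participant is doing. MCP completers and CBT completers may therefore be different kinds of people, and randomisation no longer protects their comparison.

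Two separate inferences fail. First, the completer contrast is not the effect that full compliance would produce, because that would require comparing the same people under both therapies. Second, it is not a maximum. Nothing makes the completer difference at least as large as the difference among all randomised participants.

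What is at stake is the reading of the results. If the intention-to-treat contrast were null and the completer contrast favourable, the stated rationale would give the authors grounds to present the latter as evidence of efficacy. The same section plans effect sizes for change within as well as between groups, so completer within-arm changes could also be given more weight than they can bear.

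**Working it through.** **Inputs from the protocol article.** Effect size 0.60, two-sided alpha 0.05, power 0.80, 45 per arm before dropout, 30% dropout, 59 per arm after the allowance (Sample Size). Completer definition (Data Analyses).

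**Assumed inputs, not in the article.** Correlation r between a good outcome and the tendency to complete: 0.2 to 0.5. Dropout splits between arms around the stated 30%: 30/30, 35/25 and 40/20.

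**Step 1: the plan's own figure.** A two-sample t-test with d = 0.60, alpha 0.05 and power 0.80 needs 44.6, so 45 per arm and 90 in total; power at 45 per arm is 0.804. The stated 90 reproduces.

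**Step 2: size of the completer set.** 59 × 0.70 = 41.3, so about 41 per arm.

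**Step 3: shift in one arm's completer mean.** Let outcome and tendency to complete be jointly normal, and let the fraction d with the lowest tendency drop out. The completer mean is then displaced from the all-randomised mean by

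shift = r × φ(c) / (1 − d), where c is the d-quantile of the standard normal.

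The factor φ(c)/(1 − d) is 0.350 at 20% loss, 0.424 at 25%, 0.497 at 30%, 0.570 at 35% and 0.644 at 40%. At 30% loss the shift is 0.2 × 0.497 = 0.10 SD up to 0.5 × 0.497 = 0.25 SD. It is upward only because r was taken as positive. If people leave because they feel better, it is downward.

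**Step 4: bias in MCP minus CBT.** This is the shift in the MCP arm minus the shift in the CBT arm.

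| Scenario (dropout MCP/CBT) | r = 0.2 | r = 0.5 |
|---|---|---|
| 30/30, same process in both arms | 0 | 0 |
| 35/25 | +0.03 | +0.07 |
| 40/20 | +0.06 | +0.15 |
| 25/35 | −0.03 | −0.07 |
| 20/40 | −0.06 | −0.15 |
| 30/30, leaving related to outcome in MCP only | +0.10 | +0.25 |
| 30/30, leaving related to outcome in CBT only | −0.10 | −0.25 |

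**Step 5: effect on the error rate.** With no true difference, the chance that a two-sided 5% t-test rejects at 41 per arm is the power of that test at d equal to the bias, of either sign:

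- bias 0: 0.050
- bias 0.04: 0.054
- bias 0.10: 0.073
- bias 0.15: 0.103
- bias 0.25: 0.201

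For unequal dropout the arms would not both hold 41, so those rows are approximate.

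**Step 6: is a different process in the two arms plausible?** The article does not settle it. Hypothesis (b) in the Introduction predicts greater acceptance of MCP than of CBT, and the Discussion links acceptance to adherence. The authors' own expectation therefore does not point to identical completion in both arms.

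**The case against.** The strongest reply is that the plan already deals with most of this. Intention-to-treat leads, the per-protocol analysis is an addition, the selection bias is admitted, and the conclusion is limited to compliant participants. Nothing says that the completer result may replace the main one. All of this stands, and it is why the point is minor. It does not rescue the sentence: admitting a bias does not make the conclusion valid, and limiting it to compliant participants does not identify the effect in them.

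Several stronger readings are tempting, and the article does not support them:

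- **That the completer analysis overstates efficacy.** The comparator is an active therapy, dropout is expected in both conditions and no rate by arm is given. The between-arm bias may be positive, zero or negative.
- **That within-arm change is inflated by construction.** This holds only if poor outcome and leaving go together. The article gives neither the size nor the sign of that relation.
- **That participants are removed for worsening.** The Ethics section speaks of important clinical change involving risk, which is close but not the same. It concerns termination in the study, so someone terminated during follow-up could already have completed all sessions. No frequency is given, and the section reports that no risks to participants were found.

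A reader might also ask for completion weights based on baseline variables. These would not correct leaving that depends on response during treatment, and such modelling detail may properly sit in a fuller protocol or analysis plan. Their absence is not a fault here.

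**Conclusion.** The point holds as a fault in a stated rationale. The completer comparison of MCP with CBT is not a randomised comparison, and it supports no conclusion about maximum efficacy or about the effect under full compliance. This part follows from the definition of the set and needs no numerical assumption.

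The size is illustrative. It rests on the normal selection model, the assumed correlations and the assumed splits; only the 30% dropout and the 59 per arm come from the article. Under those assumptions the bias is between 0 and about 0.25 SD in either direction, and the error rate at 41 per arm lies between 5% and about 20%. The 0.25 SD is the largest value among the scenarios examined, not a bound, and the lower scenarios leave the error rate close to 5%.

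Severity is minor. The primary analysis, the sample size and any intention-to-treat conclusion are unaffected.

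**What to change.** In the Data Analyses section:

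1. Delete the statement that per-protocol analyses allow conclusions about maximum efficacy in compliant participants.
2. State that conclusions about efficacy rest on the intention-to-treat mixed model only.
3. Describe the per-protocol analysis as a supportive, non-randomised completer analysis, and show the numbers completing and not completing treatment in each arm beside it.

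This is a change of wording plus a small table from data that the trial will hold anyway. It needs no new data and no change to the sample size. The price is a less favourable claim for completers.
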